## Abstract

**Background:**

Panic disorder with or without agoraphobia is a commonly occurring disorder affecting 2 to 3% of the population in Sweden. Untreated, panic disorder is a chronic condition that significantly increases the risk for psychiatric comorbidity, morbidity and mortality, employment difficulties, and healthcare utilization. Cognitive behavioral approaches are the recommended first-line treatment for panic disorder; however, many patients in routine care receive another evidence-based psychotherapy, including psychodynamic therapy. Allowing patients to choose among evidence-based approaches to panic disorder may improve outcomes and reduce overall health costs. Trials comparing the ‘gold standard’ treatment for panic disorder to other evidence-based psychotherapies are needed, and also trials that can separate patient preferences for treatment from randomization effects on outcome, disability and healthcare utilization in the longer term.

**Methods/Design:**

A phase 2/3 doubly-randomized controlled trial carried out in routine care with 216 adults (aged 18 to 70 years) with a primary diagnosis of DSM-IV Panic Disorder (with or without Agoraphobia). Within each clinic, patients are randomized to self-selection, random assignment of treatment, or wait-list. Patients choose or are randomly assigned to either Panic Control Treatment or Panic-Focused Psychodynamic Psychotherapy. Primary outcomes are changes in panic symptom severity, occupational status, and sickness-related absences from work at post-treatment and 6, 12 and 24 months post-treatment. Secondary outcomes include changes in agoraphobic avoidance, psychiatric comorbidity, disability, and healthcare utilization. The study also employs elements of an effectiveness trial as therapist and service-related effects on outcome will be estimated. Putative change mechanisms for the two treatments are also assessed.

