### Study aims and objectives

The primary aim of the project is to investigate the extent to which patient’s preferences for treatment influences a broad range of primary and secondary outcomes: panic symptom severity, agoraphobic avoidance, occupational status, sickness-related absences, subjective working ability, psychiatric comorbidity, panic and depression-related disability, and healthcare/medication utilization. A secondary aim is to compare outcomes for PCT, which is the form of CBT with the largest evidence base for PD, to PFPP, both of which are already delivered in routine care facilities in Sweden. A tertiary aim is to evaluate in a multivariate fashion, interactions between patient preference and other potential moderators of outcome (for example, gender, age, symptom severity, Axis I and II comorbidity, medication use, strength of the therapeutic alliance, and therapist effects). Finally we aim to evaluate putative mechanisms of change associated with each of the evaluated treatments (for example, cognitive and behavioral change, reflective capacity).

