### Primary outcome measures

Panic Disorder Severity Scale [56]Panic Disorder Severity Scale-Self Report [57]Occupational statusPatient report of the total of number of absences from work due to sickness (and compensation for the same as part of the secondary, healthcare utilization outcome)

The above outcome measures are all assessed at baseline, post-treatment and 6-, 12- and 24-month follow-ups. The total of number of absences from work due to sickness at baseline is measured as including the 3 months prior to commencing treatment.

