### Power/sample size calculations

For the planned and relatively straightforward comparisons between the 2 active treatments (PCT and PFPP) and wait-list, 25 patients per group would be needed in order to ensure an effect size (Cohen’s *d*) of 0.8 at alpha = 0.05 and power = 0.80. Our assumption of an effect size difference versus wait-list of *d* = 0.8 is conservative relative to the average controlled effect size (*d* = 1.02, 95% CI = 0.86 to 1.18) reported in a recent meta-analysis of 61 RCTs comparing psychological treatments for PD to no treatment or psychological/drug placebo [17]. For the planned and straightforward comparison between the randomized and self-selection conditions, we have assumed that the difference between the two conditions will be in the order of *d* = 0.4. Again our assumption is conservative relative to the average effect size obtained for self-selection versus randomization in preference trials involving treatments for anxiety (*d* = 0.49, 95% CI = 0.19 to 0.79), albeit based on a much smaller number of RCTs [66]. For the more complex comparisons involving the hypothesized interaction between assignment type (randomization or self-selection) and treatment type (PCT or PFPP), power calculations have been performed based on the PINT (Power IN Two-level designs, v. 2.12, September 2007) [67,68]. In the absence of *a priori* information about the size of the interaction effect between assignment and these 2 specific treatments, we assume the interaction effect size will be comparable in size to the main effect size for assignment (that is *d* = 0.40). At alpha = 0.05, power = 0.80 and *d* = 0.4, a total of 200 patients is required. Assuming a 15% drop-out rate, a total of 212 patients is required.

After consideration of issues pertaining to practicality of randomization, the target recruitment is N = 216. This was based on the following tentative assumptions, among others: Assignment (randomized versus self-selected) is a fixed effect on Level 1 with M = 0 and SD = 1; the Pre-treatment measure is a random and fixed effect on Level 1; Treatment (PCT versus PFPP) is a Level 2 predictor with M = 0.0625 (given a 55:45 distribution in the self-selection group) and SD = 1; residual variance in post-treatment = 0.70; and explained variance on outcome across therapists = 0.05.

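### Four primary measures at four times have no lead outcome or time point, while the sample size spends a full 0.05 on a single post-treatment outcome

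*Protocol article*

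**What the plan says.** The abstract (Methods/Design) gives three primary constructs and attaches four times to all of them: "Primary outcomes are changes in panic symptom severity, occupational status, and sickness-related absences from work at post-treatment and 6, 12 and 24 months post-treatment".

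The section Primary outcome measures lists four instruments: PDSS, PDSS-Self Report, occupational status, and the patient's own report of sickness absences. It adds: "The above outcome measures are all assessed at baseline, post-treatment and 6-, 12- and 24-month follow-ups". There is no ranking, no co-primary rule and no primary time point.

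Study aims and objectives does not narrow this. The primary aim is whether preference "influences a broad range of primary and secondary outcomes". That section does rank the aims: preference first, PCT versus PFPP second, interactions with other moderators third.

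Alpha appears only under Power/sample size calculations. For the wait-list comparisons, "25 patients per group would be needed in order to ensure an effect size" of 0.8. For the assignment-by-treatment interaction, "At alpha = 0.05, power = 0.80 and *d* = 0.4, a total of 200 patients is required". The listed model assumptions concern one outcome after treatment, with the pre-treatment measure as a predictor: "residual variance in post-treatment = 0.70; and explained variance on outcome across therapists = 0.05". The outcome measure is not named there.

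**The concern.** Which outcome and time point are primary is normally settled in the protocol. This article does settle it, as four measures by four times of equal standing. That leaves up to 16 results which could each be reported as the primary finding on preference. A reader of the final report could not tell a planned primary result from the most favourable of the 16.

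The sample size does not match this breadth. It makes no allowance for several primary tests. It states no power for occupational status, for absence counts or for any follow-up time, although all carry the primary label. An adjustment added later would have to come out of the stated power.

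One further choice is open. Under Randomization and allocation concealment, follow-up interviews are unblinded, and recordings are re-rated by blinded raters whose ratings will be reported. Which of the two is the primary PDSS is not said.

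**Working it through.** **Inputs from the article.** Four primary measures and four post-baseline times (Primary outcome measures). Alpha 0.05, power 0.80, d = 0.4 with total 200, and d = 0.8 with 25 per group (Power/sample size calculations). Wait-list of 3 months followed by re-randomization (same section, allocation paragraph). The article gives no correlations between measures or times, so those below are assumptions.

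**1. The plan's own figures.** For two means, n per arm = 2(z₁₋α/₂ + z₀.₈₀)²/d².
- Two-sided 0.05: 2(1.960 + 0.842)² = 15.70. For d = 0.8, 15.70/0.64 = 24.5, so 25 per group (stated 25). For d = 0.4, 15.70/0.16 = 98.1, so 99 per arm and 198 in total (stated 200).
- One-sided 0.05 would give 20 per group and 78 per arm (156 in total), which do not match.

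The figures therefore correspond to an undivided two-sided 0.05. The 200 is stated for the interaction and came from a two-level power program that cannot be rerun from the article. It was matched here only as a simple two-group comparison.

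**2. Count of possible tests.** Preference contrast: 4 × 4 = 16. Wait-list contrast: post-treatment only, because the wait-list has ended before the 6-, 12- and 24-month follow-ups, so at most 4.

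**3. Familywise error if any one test at 0.05 suffices.** Under independence, 1 − 0.95ᵏ:
- k = 16: 1 − 0.95¹⁶ = 56.0%
- k = 4: 1 − 0.95⁴ = 18.5%
- k = 1: 5%

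With correlated two-sided z-tests (200,000 simulated draws, correlation taken as between-measure × between-time):

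| Scenario | Assumed between-time correlation | Assumed between-measure correlation | Error |
|---|---|---|---|
| 16 tests | 0.3 to 0.8 | 0 to 0.5 | 33–54% |
| 16 tests | 0.9 | 0 to 0.5 | 27–33% |
| One test per measure | – | 0.3 to 0.8 | 11–17% |

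Including independence, the ranges are about 27–56% for 16 tests and about 11–18.5% for one test per measure.

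**4. Cost of a later Bonferroni adjustment.** Power = Φ(d√(n/2) − z₁₋α/₂), with n = 100 per arm and d = 0.4, so d√(n/2) = 2.828.

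| Alpha per test | Power | n per arm for 80% |
|---|---|---|
| 0.05 | Φ(2.828 − 1.960) = 81% | 99 |
| 0.05/4 = 0.0125 | Φ(2.828 − 2.498) = 63% | 140 |
| 0.05/16 = 0.0031 | Φ(2.828 − 2.955) = 45% | 181 |

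**The case against.** The strongest reply is that the article states no testing rule at all. Alpha = 0.05 is a sample-size input. Nowhere does the article say that each measure is tested at each time at that level, or that one significant result counts as success. Models over time and multiplicity procedures are commonly left to a statistical analysis plan, which is not shown. Repeated assessment of a measure does not by itself imply four separate primary tests. All of this stands. A reader might infer that the trial's actual false-positive rate is 56%, or some figure in the upper part of the 27–56% range. The documents do not support that: these are scenario figures resting on an any-one-suffices rule and on assumed correlations.

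A reader might also count 16 tests for every contrast and add the contrasts together. That fails on two grounds. The wait-list contrast cannot extend beyond post-treatment. And the aims are already ranked, so preference, PCT versus PFPP and the moderator interactions are not equal claims.

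Finally, it would be tempting to say that the sample size already points to blinded PDSS at post-treatment for self-selection versus random assignment. It does not. The power section names neither the PDSS nor blinded ratings, and gives the 200 for the interaction. The main effect of assignment shares only the assumed d = 0.4.

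What the reply does not remove is the designation itself. The ranking of aims orders the contrasts but not the outcomes within a contrast. An unseen analysis plan could add an adjustment, but the published sample size leaves no room for one.

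**Conclusion.** The point holds as a poorly fixed primary endpoint, not as a demonstrated error rate. Four measures at four times are equally primary, no lead outcome or time is named, and the sample size corresponds to one outcome tested at a full two-sided 0.05.

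For the preference contrast, the consequence runs from 5% if a single lead test is designated, through about 11–18.5% with one test per measure, to as much as 56% if all 16 are tested and any one suffices. For the wait-list contrast the ceiling is 18.5%. The values below 18.5% and 56% rest on correlations the article does not give. This should be corrected: it determines what the trial can claim as its primary result, and the change is one of wording.

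**What to change.** Designate one lead primary outcome and one time point for the primary aim, self-selection versus random assignment, tested at two-sided 0.05. Blinded-rater PDSS at post-treatment is one reasonable choice. It would also settle whether the blinded or the unblinded rating is primary. It should be presented as a choice, and the power section should then name the same outcome, time and contrast.

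Test the remaining primary measures and times in a prespecified order, each at 0.05 only if the preceding step succeeds, or label them secondary. The order is the sponsor's to choose. Given the article's emphasis on work disability, the sponsor may want occupational status or absences early in it.

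The cost is wording in the outcomes and power sections and a matching registry entry, with no added patients. Recruitment was still under way at 138 patients and follow-up was planned to end in 2018, so the change could precede the final data. The downside is that work outcomes placed later in the order can be claimed as confirmatory only if the earlier steps succeed.

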**Discussion:**

Cognitive behavioral and psychodynamic therapies are both evidence-based approaches that are routinely offered to panic disordered patients in Sweden. However, little is known about the relative effectiveness of these two approaches for panic/agoraphobia, work-related disability and healthcare utilization over the longer term. The current trial (POSE) also addresses the important but understudied issue of whether patient preference for a particular psychotherapeutic approach moderates outcome.

**Trial registration:**

ClinicalTrials.gov NCT01606592 (registered 19 March 2012).

## Background

Panic Disorder (PD) without Agoraphobia as defined in the 4th edition of the *Diagnostic and Statistical Manual for Mental Disorders* (DSM-IV) (American Psychological Association, 2000) involves recurrent, unexpected panic attacks with at least one attack followed by persistent concerns or worries about additional attacks, and/or significant changes in behavior related to the attacks. PD with Agoraphobia involves the additional requirement that the individual avoids or endures with marked distress (often necessitating a companion to accompany them) places or situations from which it might be difficult (or embarrassing) to escape and/or to receive help in the event of a panic attack [1]. In DSM-V, the two disorders are de-linked so that individuals with both PD and Agoraphobia receive two diagnoses [2]. As this study commenced prior to the publication of DSM-V, we used the DSM-IV criteria with treatment focused on patients with a primary diagnosis of PD - with or without Agoraphobia.

In accordance with prevalence studies carried out elsewhere [3,4], the 12-month prevalence of PD in Sweden is 2 to 3% and one of the most frequent causes of illness among Swedes aged 15 to 44 years [5]. When untreated, PD is a chronic and debilitating condition associated with an increased risk of psychiatric comorbidity, health complaints, low quality of life, diminished capacity for work, morbidity and mortality, a heavy burden on the family, and significantly increased healthcare utilization [5-10]. The presence of PD, especially with agoraphobia, is recognized as a major obstacle to Swedish adults returning to work after a period of sick leave and to young people attempting to enter the labor force for the first time (50% of whom with PD fail to do so) [5]. When last estimated (1996), the total cost of PD in Sweden was estimated at 1.7 billion euros per annum [5]. Effective treatment of PD has been shown to reduce the cost of care by as much as 94% [11].

Cognitive behavioral therapy (CBT) and pharmacotherapy are the recommended treatments for adults with PD in many countries [12-14] and the same is true in Sweden [5]. Numerous meta-analyses have been carried out and overall they find that both treatments, either alone or in combination, yield large effect sizes when compared with no/minimal treatment and medium effect sizes relative to psychological/drug placebo in the acute phases of treatment [15-17]. Effect sizes beyond 12 to 24 months are generally more modest than at post-treatment or 6 month follow-up, particularly for (mono) pharmacotherapy, with little evidence of further symptomatic improvement during the follow-up period [14-18]. The use of pharmacotherapy alone is also associated with a significantly increased risk of attrition during treatment and relapse when treatment is discontinued [15,19]. Thus, there is an emerging consensus that CBT should be offered first to PD patients and to those discontinuing pharmacotherapy [5,14,15,17]. Whether another evidence-based psychotherapy could also be offered remains unclear, as there have been extremely few trials involving PD patients and comparisons between CBT and an active psychological treatment [20].

The longer-term efficacy of CBT for PD also remains unclear [17,21]. Across randomized controlled trials (RCTs) the median length of follow-up is 6 months with few trials reporting findings past 12 months. Also, few trials involve designs that permit continued comparison between treatments or between treatment and control groups during the follow-up period. Conclusions about longer-term efficacy are further confounded by significant attrition and treatment-seeking during the follow-up period.

Durham *et al*. [21] carried out a 2- to 14-year follow-up of participants in 8 RCTs of CBT for anxiety, 4 of which focused on PD and the others on Generalized Anxiety and Post-Traumatic Stress Disorders (PTSD). Of those initially treated with CBT for PD, only 40% achieved sustained recovery (defined as the absence of any anxiety disorder) without the benefit of additional treatment (any) during the follow-up period. Even with additional treatment, only 54% of those initially treated with CBT for PD achieved long-term recovery [21]. Across all of the RCTs, ‘recovered’ patients had significantly worse scores on all subscales of the Brief Symptom Inventory, with most suffering from mild symptoms that were slightly disabling and 20% falling just below threshold for diagnosis. More favorable findings can be found in a recent multi-center RCT by Gloster *et al*. [22] comparing 2 forms of CBT for PD as 74% of patients who were responders at post-treatment retained this status at 24 months. However, 37.5% of all CBT treated patients sought further treatment between 6 and 24 months and this was unrelated to anxiety severity at 6 months. Further favorable findings are available from an earlier uncontrolled study of PD patients treated with CBT wherein 82% of initial treatment responders remained in remission at 5 or more years post-treatment and 62% at 10 years or more [23]; however, the patients were less ill to begin with.

It is important to note that most RCTs involving PD patients have focused primarily on changes in symptoms (panic, agoraphobia, and depression) and general indices (often clinician-rated) of overall impairment. Less is known about the impact of evidence-based approaches on the other aspects of disability that usually accompany PD such as absences from work due to sickness, difficulties returning to work and increased healthcare utilization [24]. Reducing symptoms *per se* does not necessarily improve these aspects of functioning [24-26]. There is some evidence that short-term therapies are less effective than longer therapies on improving return to work after sick leave in depressed and anxious patients [24,27]. However, the general move in health services overall is towards briefer, not longer, psychological treatments.

What about attrition in CBT and pharmacotherapy? PD patients fear somatic symptoms and often the medical side effects that can accompany pharmacotherapy, and these fears may represent a major reason why PD patients often refuse medication when first offered (pre-treatment attrition) or why as many as one third prematurely discontinue pharmacotherapy once begun [28,29]. Limited data is available about pre-treatment attrition in relation to CBT. In a study of 731 patients (22% with PD) presenting to a specialist anxiety service, all of whom were offered CBT outside of a clinical trial, the authors found that 30% dropped out before commencing CBT with 12.6% actively refusing CBT [30]. Although drop-out from CBT once begun was relatively low in the previous study (10.7%), a meta-analysis of RCTs by Haby *et al*. involving patients with either primary PD, Generalized Anxiety Disorder, or depression reported an average drop-out rate of 17% for PD patients treated with CBT (range = 0 to 54%) [18].

The dominance of CBT in the treatment of anxiety over the past two decades has meant that relatively few RCTs have been carried out comparing this approach to another active psychological treatment [31,32]. The majority of comparative psychotherapy trials for patients with PD have involved two forms of CBT (for example, cognitive versus behavioral, with/without therapist-guided exposure, self-help, Internet-based, and so on). Psychodynamic therapy (PDT) is an evidence-based treatment for a range of conditions involving a significant anxiety component [32,33]. While much fewer RCTs of PDT exist than for CBT, meta-analytic reviews have been carried out to estimate the effectiveness of PDT for a range of problems including anxiety [34-38]. In the 2 most recent [35,36], PDT was observed to be no less effective for anxiety than other active treatments in the short or long term, had similar drop-out rates (17%) as reported for CBT, and yielded controlled effect sizes relative to no/minimal treatment or treatment as usual in the medium range (*g* = 0.63). These effects were persistent at follow-ups of 6 to 12 months; however, the limited number of trials (focused primarily on social anxiety) and the significant heterogeneity between trials limits the conclusions that can be drawn [36]. Further comparative trials involving PDT and CBT are needed [13].

Milrod *et al*. [39] have developed a brief form of PDT titled *Panic-Focused Psychodynamic Psychotherapy* (PFPP). In an open trial of PFPP with 21 panic disordered patients (most with comorbid agoraphobia), 16 (76%) experienced a remission of their panic/agoraphobic symptoms at post-treatment with gains maintained at 6 months [40,41]. In a subsequent RCT involving 49 PD patients, those receiving PFPP were significantly more likely to have their panic symptoms remit at termination than patients receiving applied relaxation training (73% versus 39%) with PFPP gains (and differences between the groups) maintained at 12 months [42]. PFPP was well-tolerated with only 7% withdrawing prematurely as compared to 34% in the applied relaxation condition. More recently, Beutel *et al*. carried out a randomized controlled trial of PFPP and CBT (plus exposure) delivered in routine care to 54 patients with PD (the majority with agoraphobia) [43]. Remission rates at post-treatment were 44% for PFPP rising to 50% at 12-month follow-up compared to a 66% remission at post-treatment for CBT decreasing to 56% at follow-up. The differences between the two treatments were non-significant.

While further comparative trials between PFPP and CBT for PD are clearly needed, Brewin and Bradley [44] have argued that RCTs comparing two or more treatments may give misleading results if patients’ preferences for the offered treatment alternatives are not controlled for. Thus, to the extent that patients’ preferences reflect their suitability for a specific type of psychotherapy, the one that is the most suitable for the majority of the patient population will appear superior, even if the treatments are equally effective. In a qualitative follow-up study of patients who had received CBT and PDT, patients who had unsuccessful treatment felt they had received a form of therapy that was less suitable to their individual needs and disposition and had well-developed ideas about how a more effective treatment should have been carried out [45]. A series of studies have shown that most people given adequate information will voice definite ideas about the kind of treatment that might be most suitable to their needs: so-called ‘helpfulness beliefs’ [46-48]. The resulting preferences are significantly moderated by the patient’s previous experiences with psychotherapy or psychiatry in general and generate a distribution of what may be a proxy for the ‘suitability differential’ between different forms of psychotherapy [48].

So, in a trial comparing two or more treatments where patients are allowed to select their preferred evidence-based treatment, one might reasonably predict little or no difference between the treatment groups. Also, if one assumes that outcome is at least partly moderated by the quality of the treatment alliance, one might reasonably expect stronger effects generally for treatments that were patient-selected than randomly assigned. It is possible to separate the effects of patient preference from the effects of randomization (that is treatment) by using a hybrid, double-randomization design [49]. In such a trial patients are randomized to self-selection or random assignment of treatment conditions.

While patient preferences have drawn considerable attention as a potential moderator of treatment outcome [46-48,50,51], no such hybrid randomized controlled study (comparing treatment and preference effects) has yet been published for PD patients. A recent study by Watzke *et al*. [52] compared systematic treatment selection to randomized assignment of treatment, either non-protocol CBT or PDT, on outcomes for a wide range of disorders (including anxiety) in 291 inpatients. In the systematic treatment selection condition, the inpatient team arrived at a consensus decision about the most appropriate treatment based on diagnosis, psychometric assessment, capacity for self-reflection, and patient goals. The authors found no overall differences in outcome between patients in the randomized assignment and systematic treatment selection conditions. Patients who were systematically assigned to PDT had better long-term outcomes than patients who were randomly assigned to this same treatment but no such effects were found for CBT.

The role of patient preference for a particular evidence-based approach is better illustrated in a recent hybrid RCT preference trial by Le *et al*. [53]. The investigators randomized 218 patients with a primary diagnosis of PTSD to patient-preference or randomly-assigned treatment conditions involving either prolonged exposure therapy (a form of CBT) or sertraline. Overall, giving patients a choice over treatment yielded significantly lower health costs and more quality-adjusted life years (QALYs) than random assignment to treatment conditions. Interestingly, prolonged exposure therapy was less costly and yielded more QALYs relative to sertraline when the treatment was assigned rather than chosen.

CBT and pharmacotherapy are currently the ‘gold standard’ treatments for PD. Pharmacotherapy will remain an important treatment option for many patients but pre- and post-treatment attrition for pharmacotherapy remains a significant concern. CBT is clearly an effective approach for PD but not for every patient and longer-term gains remain somewhat unclear. Also, the state of the literature is such that those advocating for the increased use of CBT in routine care for patients with PD will struggle to point to data showing its incremental effectiveness over other evidence-based psychotherapies that are also routinely provided in mental health services. Increasingly, both healthcare service providers and treatment guidelines have recommended that patients be encouraged and supported in choosing between various treatment options and being more active in the way treatment is delivered. It is possible that allowing patients to choose among evidence-based approaches may improve outcomes and reduce the overall burden and cost of illness. Further trials are needed involving comparisons between CBT and other evidence-based psychological approaches to help patients make better, data-informed choices about which treatment is likely to work best for them in the short and longer term.

